### Outcome

The outcome variable is mortality within 1 year of admission, which will be modelled as a binary variable. This will be ascertained through linkage to a population-based registry, the Registered Persons Database, which is maintained by the Ontario Ministry of Health and Long-Term Care. This contains a historical listing of all healthcare numbers that have been issued under Ontario’s universal health insurance program, demographic information (i.e., age, sex, postal code), and vital status, including date of death.

### Sample size

The cohort includes approximately 298,000 patients. It will be split temporally into derivation and validation cohorts. The derivation cohort will comprise about 235,000 patients (~ 80%), hospitalized from 2009 to 2017, and the validation cohort will comprise about 63,000 patients (~ 20%), hospitalized from 2018 to 2019.

A major consideration in prediction modelling is overfitting, which happens in the context of including a disproportionately high number of degrees of freedom in the model relative to the number of events in the cohort. For a binary logistic regression model, the number of participants in the smaller of the two outcome groups should be at least 10 times higher than the number of degrees of freedom in the model [35]. The derivation cohort includes about 82,000 deaths within 1 year of admission. Therefore, the maximum number of degrees of freedom is expected to be significantly higher than the number in the prespecified model, such that overfitting is unlikely. We calculated the minimum sample size using the *pmsampsize* package in R according to the approach proposed by Riley et al. [36, 37]. Assuming a conservative c-statistic of 0.77 [23], an event proportion of 0.35, 205 parameters, and a shrinkage factor of 0.90, the minimum recommended sample size is 8251. The expected sample size surpasses this recommendation, and as a result, we anticipate having a sufficient sample size. It has also been recommended that there be at least 100 events and 100 non-events in a validation cohort [38]. The validation cohort includes about 21,000 deaths within 1 year of admission. Therefore, we will have the minimum number of events and non-events.

### Analysis plan

The analysis plan was informed by guidelines for regression modelling [39] and clinical prediction models [35] after accessing the derivation dataset but before model fitting or analyses of predictor-outcome associations. Key considerations of the analysis plan are full prespecification of predictor variables and avoidance of data-driven variable selection, and use of flexible functions to model continuous predictors. Analyses will be conducted using SAS Enterprise Guide V.9.4. The reporting of the model will be guided by the TRIPOD statement for multivariable prediction models for prognosis [29].

#### Identification of predictors

The predictor variables have come from 3 sources. First, variables used in the modified Hospital One-Year Mortality (mHOMR), most of which are available in the DAD, will be included in the initial model. This prognostic tool was established to predict mortality 1 year after hospitalization [40]. Though it was not specifically created for patients with dementia, we judged it to serve as an ideal framework on which to build our model for several reasons. First, it was derived from and internally validated in Ontario, demonstrating high discrimination and calibration [40], and has been externally validated in a temporally distinct population in Ontario and two geographically distinct populations in Alberta, Canada, and Boston, Massachusetts, demonstrating high discrimination and calibration [41]. Second, it was judged to be both a feasible [42] and acceptable [43] tool for mortality risk prediction by patients, caregivers, and healthcare providers. Third, a high mHOMR score has been associated with unmet palliative care needs [44]. Finally, a version of mHOMR has been successfully implemented in several Ontario hospitals.

Second, we identified variables in existing prognostic indices [23–25] or that have an established association with mortality based on etiological studies [45–57] among hospitalized patients with dementia. The existing prognostic indices were identified through a systematic review using a single electronic database (PubMed), in addition to hand-searching of each of their reference lists. The etiological studies were identified in a recent scoping review of prognostic factors in dementia [58]. We then identified, where possible, correlates of these variables in the DAD. Finally, we reviewed all variables in the DAD to identify those that, based on subject-matter expertise, could inform mortality risk prediction in this patient population but are not present in either the mHOMR or the literature. Specifically, our research team includes clinical expertise in internal medicine, family medicine, public health, and palliative medicine. Since the ultimate objective is to have the clinical tool generate a risk of 1-year mortality at the time of admission, predictor variables that would not be known at the time of admission (e.g., admitting diagnosis, length of stay) were not considered. Variables with narrow distributions or insufficient variation will be excluded (e.g., binary variables for which one level has few or no observations). Variables with a high proportion of missing values (> 50%) will be excluded. While multiple imputation (see Missing data) may perform well if a variable has > 90% missingness [59], a variable with > 50% missing may be of poor quality and result in bias. A total of 87 predictor variables were identified and categorized as follows: sociodemographic factors (3), comorbidities (51), previous interventions (8), functional status (11), nutritional status (7), admission information (4), previous health care utilization (3) (Table 1). For comorbidities and previous interventions, a 3-year lookback window will be used, which is in keeping with the most recent iteration of the mHOMR [60].

**Table 1 Tab1:** Prespecification of predictor variables for a mortality risk prediction tool among hospitalized patients with dementia with initial degrees of freedom allocation

Variable	Scale	Initial variable specification	Degrees of freedom
Sociodemographic factors			
Age	Continuous	5-knot spline: valid range: 65 to 105 years	4
Sex	Categorical	Male; female	1
Living status	Categorical	5 categories: home, independent; home, home care; nursing home; rehabilitation; chronic hospital	4
Comorbidities			
Cerebrovascular disease	Categorical	Yes; no	1
Heart failure	Categorical	Yes; no	1
Cardiovascular disease	Categorical	Yes; no	1
Arrhythmia	Categorical	Yes; no	1
Cardiac arrest	Categorical	Yes; no	1
Chronic obstructive pulmonary disease	Categorical	Yes; no	1
Asthma	Categorical	Yes; no	1
Pneumonia	Categorical	Yes; no	1
Pneumonitis	Categorical	Yes; no	1
Adult respiratory distress syndrome	Categorical	Yes; no	1
Interstitial lung disease	Categorical	Yes; no	1
Respiratory failure	Categorical	Yes; no	1
Gastrostomy site infection	Categorical	Yes; no	1
Liver cirrhosis	Categorical	Yes; no	1
Urinary tract infection	Categorical	Yes; no	1
Fecal incontinence	Categorical	Yes; no	1
Urinary incontinence	Categorical	Yes; no	1
Renal failure	Categorical	Yes; no	1
Decubitus ulcer	Categorical	Yes; no	1
Parkinson’s disease	Categorical	Yes; no	1
Multiple sclerosis	Categorical	Yes; no	1
Osteoporosis	Categorical	Yes; no	1
Fracture	Categorical	Yes; no	1
Malignancy			
Lip, oral cavity, pharynx	Categorical	Yes; no	1
Digestive organs	Categorical	Yes; no	1
Respiratory, intrathoracic organs	Categorical	Yes; no	1
Skin	Categorical	Yes; no	1
Mesothelium, soft tissue	Categorical	Yes; no	1
Breast	Categorical	Yes; no	1
Female genital organs	Categorical	Yes; no	1
Male genital organs	Categorical	Yes; no	1
Urinary tract	Categorical	Yes; no	1
Central nervous system	Categorical	Yes; no	1
Endocrine glands	Categorical	Yes; no	1
Bone	Categorical	Yes; no	1
Unspecified	Categorical	Yes; no	1
Blood	Categorical	Yes; no	1
Multiple	Categorical	Yes; no	1
Sepsis	Categorical	Yes; no	1
Diabetes mellitus	Categorical	Yes; no	1
Hypertension	Categorical	Yes; no	1
Peripheral arterial disease	Categorical	Yes; no	1
Shock	Categorical	Yes; no	1
Mood disorder	Categorical	Yes; no	1
Schizophrenia	Categorical	Yes; no	1
Complication from benzodiazepine	Categorical	Yes; no	1
Complication from antipsychotic	Categorical	Yes; no	1
Fall	Categorical	Yes; no	1
vChronic kidney disease	Categorical	Yes; no	1
Rheumatoid arthritis	Categorical	Yes; no	1
Polypharmacy	Categorical	Yes; no	1
Previous interventions			
Heart resuscitation	Categorical	Yes; no	1
Mechanical ventilation lasting ≥ 96 h	Categorical	Yes; no	1
Mechanical ventilation lasting < 96 h	Categorical	Yes; no	1
Dialysis	Categorical	Yes; no	1
Cardioversion	Categorical	Yes; no	1
Chemotherapy	Categorical	Yes; no	1
Radiotherapy	Categorical	Yes; no	1
Tracheostomy	Categorical	Yes; no	1
Functional status			
Hospital Frailty Risk Score	Continuous	5-knot spline: valid range 0 to 99	4
Dysphasia and aphasia	Categorical	Yes; no	1
Dysarthria and anarthria	Categorical	Yes; no	1
Dysphagia	Categorical	Yes; no	1
Dependence on wheelchair	Categorical	Yes; no	1
Blindness	Categorical	Yes; no	1
Hearing loss	Categorical	Yes; no	1
Hospital-based occupational therapy consultation in past 3 years	Categorical	Yes; no	1
Hospital-based physiotherapy consultation in past 3 years	Categorical	Yes; no	1
Hospital-based social worker consultation in past 3 years	Categorical	Yes; no	1
Hospital-based speech language pathology consultation in past 3 years	Categorical	Yes; no	1
Nutritional status			
Weight	Continuous	5-knot spline	4
Height	Continuous	5-knot spline	4
Parenteral nutrition	Categorical	Yes; no	1
Feeding tube	Categorical	Yes; no	1
Anorexia	Categorical	Yes; no	1
Abnormal weight loss	Categorical	Yes; no	1
Volume depletion	Categorical	Yes; no	1
Admission information			
Admitting service	Categorical	15 categories: General internal medicine; Cardiology; Gastroenterology; Palliative care; Medical oncology; General surgery; Cardiovascular surgery; Neurosurgery; Orthopedic surgery; Plastic surgery; Thoracic surgery; Trauma; Urology; Gynecology; Psychiatry	14
Admission urgency	Categorical	3 categories: elective; urgent, without ambulance; urgent, with ambulance	2
Admission directly to ICU	Categorical	Yes; no	1
Urgent 30-day readmission	Categorical	Yes; no	1
Previous healthcare utilization			
ED visits in past 12 months	Ordinal	7 categories: 0, 1, 2, 3, 4, 5, 6 +	6
Admissions by ambulance in past 12 months	Ordinal	4 categories: 0, 1, 2, 3 +	3
Hospital-based palliative care in past 3 years	Categorical	Yes; no	1

Age will be interacted with all variables except those listed under sociodemographic factors, admission information, and previous health care utilization; renal failure will be interacted with dialysis; each site of malignancy will be interacted with chemotherapy

*ICU* Intensive care unit, *ED* Emergency department

The model will include age interactions with variables that represent comorbidities and previous interventions, since the association of these variables with mortality may vary with age. It will also include interactions of diseases with corresponding treatments, including kidney dysfunction with dialysis, and malignancy with chemotherapy.

#### Data cleaning and coding of predictors

All variables will be evaluated for potentially invalid values. Specifically, continuous variables will be inspected using descriptive statistics and boxplots. Categorization of continuous variables will be avoided to prevent loss of predictive information. Categorical variables will be inspected using frequency distributions. Should invalid values be identified, then they will be corrected, if possible, and otherwise, set to missing. All data cleaning and coding will be performed before analyzing predictor-outcome associations.

#### Missing data

Missing values will be imputed with multiple imputation methods. This is in contrast to complete case analysis, which suffers from inefficiency and selection bias [35]. Multiple imputation is performed in 3 main steps [61, 62]. First, an imputation model is established to impute missing values using random draws from the conditional distribution of the missing variable based on all the other variables in the analytic model. This imputation is performed *M* number of times, which is contingent on the proportion of missing values. It has been recommended that *M* be ≥ 100 × *p*, where *p* is the proportion of missing values [63]. This step creates *M* number of imputation datasets, each with different imputed values, which accounts for the uncertainty associated with imputation. Second, logistic regression will be performed in each of the *M* imputation datasets, each resulting in different parameter estimates. Finally, the parameter estimates will be combined to generate the final parameter estimates of the analytic model [64]. This will be performed using the MI [65] and MIANALYZE [66] functions in SAS.

#### Model specification

Continuous variables will be flexibly modelled using restricted cubic splines, with knots placed at fixed quantiles of distribution (e.g., in a five-knot spline function, 5th, 27.5th, 50th, 72.5th, and 95th). Categorical variables with levels that include a low number of observations will be combined with others. Interactions will be restricted to linear terms. The initial model includes a total of 205 of degrees of freedom, 111 of which are of main effects and 94 of which are of interaction effects.

The predictive potential of each variable will be determined by a method described by Harrell [39]. Specifically, a general effects model will be created that includes all predictor variables. The degrees of freedom of each variable will be subtracted from its *χ*(2) statistic to level the playing field given that the variables have varying degrees of freedom. These values will be plotted from highest to lowest. Variables with higher predictive potential will retain their initial degrees of freedom; whereas those with lower predictive potential will be modelled as simple linear terms or have their infrequent categories combined. This does not increase the type 1 error rate since all predictor variables will be retained in the final model regardless of their strength of association with the outcome variable.

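### The stated model size of 205 degrees of freedom, also the parameter count behind the minimum sample of 8251, does not agree with Table 1, which with its footnote gives 123 + 93 = 216

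*Protocol article*

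**What the plan says.** All places are in the protocol article.

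- **Model specification** describes the initial model as having "a total of 205 of degrees of freedom, 111 of which are of main effects and 94 of which are of interaction effects". The same section allows only linear terms in interactions, so each interaction with a single-term or binary variable costs 1 df.
- **Sample size** carries this count forward: "205 parameters, and a shrinkage factor of 0.90, the minimum recommended sample size is 8251". The other inputs are a c-statistic of 0.77 and an event proportion of 0.35.
- **Identification of predictors** lists 87 variables: "sociodemographic factors (3), comorbidities (51), previous interventions (8), functional status (11), nutritional status (7), admission information (4), previous health care utilization (3).
- **Table 1** allots df to each variable. Age ("5-knot spline: valid range: 65 to 105 years") and the Hospital Frailty Risk Score ("5-knot spline: valid range 0 to 99") have 4 df each, as do weight and height, which are also 5-knot splines.
- **The Table 1 footnote** defines the interactions: "Age will be interacted with all variables except those listed under sociodemographic factors, admission information, and previous health care utilization"; in addition, "renal failure will be interacted with dialysis; each site of malignancy will be interacted with chemotherapy".
- **The paragraph after Table 1** says: "The model will include age interactions with variables that represent comorbidities and previous interventions". It then refers to kidney dysfunction with dialysis, where the footnote names renal failure only.

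**The concern.** The main-effect and interaction counts can both be checked against Table 1, and neither agrees. The table and its footnote also differ from the sentence that follows on which variables interact with age.

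What is at stake is the specification. The Analysis plan section makes full prespecification of predictors a key feature and says the plan was written after the derivation data had been accessed, though before any model was fitted. The Background criticises existing tools for lacking non-linear and interaction terms, and the Objectives promise them here. Those are the terms whose number or membership is unclear. All predictors are to be retained, and the final model keeps the derivation specification. Two analysts working from this article could therefore fit models that differ by 18 age interactions, including age by frailty score and age by weight.

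**Working it through.** **1. Main effects, from the df column of Table 1**

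| Group | Variables | df |
|---|---|---|
| Sociodemographic | 3 | 4 + 1 + 4 = 9 |
| Comorbidities (15 of them malignancy rows) | 51 | 51 |
| Previous interventions | 8 | 8 |
| Functional status | 11 | 4 + 10 = 14 |
| Nutritional status | 7 | 4 + 4 + 5 = 13 |
| Admission information | 4 | 14 + 2 + 1 + 1 = 18 |
| Previous utilization | 3 | 6 + 3 + 1 = 10 |
| **Total** | **87** | **123** |

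The variable counts match the text group by group, so no row was lost when the table was read. The stated main-effect count is 111, which is 12 lower.

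**2. Interactions, 1 df each**

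- Footnote list: age terms 51 + 8 + 11 + 7 = 77; renal failure by dialysis 1; malignancy by chemotherapy 15. Total 77 + 1 + 15 = 93, against the stated 94.
- Sentence after the table, read as exhaustive: age terms 51 + 8 = 59; total 59 + 1 + 15 = 75.
- Adding chronic kidney disease by dialysis raises these to 94 and 76.

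**3. Totals that keep the Table 1 df column**

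| Interaction list | Renal failure only | Plus chronic kidney disease |
|---|---|---|
| Footnote | 123 + 93 = 216 | 123 + 94 = 217 |
| Sentence, if exhaustive | 123 + 75 = 198 | 123 + 76 = 199 |

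None equals 205.

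**4. Where 205 may come from (inference)**

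Counting the four 5-knot splines as 1 df each removes 4 × 3 = 12 df, and 123 − 12 = 111. Adding chronic kidney disease by dialysis to the footnote list gives 94. Together, 111 + 94 = 205.

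**5. Sample size, reproducing the stated figure first**

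The shrinkage criterion of the Riley approach is n = P / [(S − 1) ln(1 − R²/S)], with S = 0.90. Assuming a linear predictor that is normal within each outcome group, c = 0.77 and an event proportion of 0.35 give a Cox–Snell R² of 0.1983. For P = 205:

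n = 205 / [(−0.1) × ln(1 − 0.1983/0.90)] ≈ 8,235.

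This is 0.2% below the stated 8251. The other two criteria give about 4,955 and 350 and do not bind. The stated figure is therefore reproduced for its stated inputs.

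n is proportional to P, so the stated figure can be scaled:

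| P | Scaled from 8251 | Direct formula | Scaled change |
|---|---|---|---|
| 216 | 8251 × 216/205 = 8,694 | 8,677 | +5.4% |
| 217 | 8251 × 217/205 = 8,734 | 8,717 | +5.9% |
| 198 | 8251 × 198/205 = 7,969 | 7,954 | −3.4% |

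**6. Adequacy**

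The derivation cohort has about 235,000 patients and 82,000 deaths. 235,000 / 8,734 ≈ 27, and 82,000 / 216 ≈ 380 deaths per df. With R² = 0.1983, the expected heuristic shrinkage is 0.996 for both 205 and 216 parameters.

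**The case against.** Four points can fairly be made in the protocol's defence.

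- **The sentence after the table is not restrictive.** It contains no limiting word and may be an incomplete summary of the footnote, which states its exclusions explicitly. The stated 94 is one term from the footnote count and 19 from the narrow reading. This stands: a reader might infer that the article prescribes two different models, and the text does not go that far. It leaves 18 terms unclear and gives a good indication of which list is meant.
- **8251 is not a miscalculation.** This also stands. A reader might infer that the sample-size arithmetic is wrong or the cohort too small; neither follows. Even the direction of the correction depends on the interaction list.
- **The source of 111 is not established.** Counting splines as 1 df fits, but so would leaving out the frailty score, weight and height (4 + 4 + 4 = 12), or reducing admitting service from 14 df to 2. The spline explanation should not be reported as fact.
- **The count is only for the initial model.** Weaker predictors may later be simplified, and sparse or largely missing variables dropped, so the fitted model may have neither 205 nor 216 df. That is true, but it does not explain the mismatch: Table 1 and Model specification both describe the allocation before any simplification.

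**Conclusion.** The inconsistency is real and follows from the article's own figures. The stated 205 df (111 + 94) conflicts with Table 1 and its footnote, which give 216 (123 + 93), and no reading that keeps the table's df column yields 205. The main-effect gap is 12 df and the interaction gap is 1. Separately, the text leaves it unclear whether 18 functional and nutritional age interactions belong to the model, with the footnote the more likely intention.

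The effect on the stated minimum sample runs from about −3% to +6% and has no bearing on adequacy. The weight of the point lies in prespecification and reproducibility, and it merits correction on those grounds.

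The df counts need no assumption beyond linear interactions at 1 df each. The revised minimum samples assume the stated c-statistic, event proportion and shrinkage. They are scaled from 8251 and are not package output.

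**What to change.** Before model fitting:

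1. Keep one interaction list, the Table 1 footnote, and extend the sentence after the table so that it also covers functional and nutritional variables.
2. State whether chronic kidney disease by dialysis is included, and use the same kidney term in the footnote and the text.
3. Restate the initial model in Model specification as 123 + 93 = 216 df, or 123 + 94 = 217 if that term is included. If 111 main-effect df is really intended, correct the Table 1 df column instead, and say which variables change.
4. Rerun *pmsampsize* with the reconciled count and replace both 205 and 8251 in the Sample size section. Expect about 8,694 for 216 or 8,734 for 217.

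The cost is a few lines of wording and one software run. Recruitment, data and the conclusion on sample size do not change.

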#### Model estimation

The model will be estimated using a binary logistic regression. All predictor variables will be centered about their means. Multi-collinearity will be assessed using variable clustering using the VARCLUS function in SAS [67]. In addition, the variance inflation factor (VIF) will be calculated for each predictor variable. Predictors with a VIF > 2.5 will be judged to be potentially collinear. These methods will be used to understand the model with more clarity though will not result in further model specification.

Overfitting will be assessed visually using the calibration plot (see Assessment of performance), and statistically using the heuristic shrinkage estimator [68]. If the estimator is less than 0.9, then this suggests the presence of overfitting that requires adjustment, including shrinkage of the parameter estimates. This is unlikely considering prespecification of the model, and the low number of degrees of freedom in the model relative to the high number of events in the cohort. We intend to have the model provide an automatic calculation of mortality risk, not to have it used manually to calculate risk (see Model presentation). Therefore, predictive accuracy will be prioritized over parsimony, and a reduced model will not be estimated.

The model will be developed and validated using temporally split samples; however, the final regression coefficients will be based on the full sample. The final model will have the same specifications as the derivation model.

